#### Secondary measures

2.9.2

Secondary outcomes are: (a) a change in QoL in Ghanaian adults with T2DM who participate in a 12‐week PA programme, compared to those who receive usual diabetes care, (b) feasibility of implementation, determined by measures of safety (c) feasibility of implementation, determined by measures of participation.

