#### Exercise participation and complications

2.10.6

Data regarding participation in the PA programme will be collected. This includes the type of exercise, duration, intensity and frequency of those exercises. Data regarding exercise‐related complications will also be collected. The PT will collect such data from participants in the IG each week during their visit to the physiotherapy department and during the week‐12 follow‐up visit.

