Safety outcomes will be assessed by examining participant's subjective reports relative to possible pain, injury, medical emergencies and other exercise‐related complication that may be encountered during participation in the PA program. Safety and participation rate will be assessed as a composite of any adverse events recorded as part of the PT's checklist for exercise participation and safety and the participants' exercise diary.

At the end of each training session, the Borg Rating of Perceived Exertion (RPE) scale will be used to assess perceived exercise tolerance and exercise fatigue (Liguori et al., 2021). Schedule of visits for the RCT are outlined in Figure 1.

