### Sample size

2.12

Feasibility studies are designed to obtain preliminary data (Eldridge et al., 2016). Billingham et al. (2013) examined sample size for feasibility RCTs and found a median sample size of 72 (36 per arm). They concluded that while it is important to justify sample size in feasibility RCTs, calculating sample size may not be appropriate. Thus, this proposed study will aim for a sample of 72 participants. To account for attrition, a 20% adjustment will be added. Therefore, the target sample size for this feasibility study will be 90 participants: 45 in each group.

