### Data analysis

2.13

Data analysis will be performed using the latest version of STATA. Feasibility outcomes will be summarised using descriptive statistics such as frequencies, percentages, mean, SD, median and interquartile range. Relevant parametric and non‐parametric repeated measure analyses will be undertaken to measure between groups differences and changes in effect between and within the two groups. Specifically, the student's *t*‐test will be used for comparing the IG and CG. Between group analysis will be conducted using Pearson's chi‐square and Mann‐Whitney tests for categorical and continuous variables, respectively. A *p*‐value of <0.05 will be considered statistically significant. To obtain the overall effect of the PA intervention on MetS markers, the MetS score for each participant will be assessed. The MetS score is a useful measure of MetS severity, and it correlates to the severity of CVD (Solymoss et al., 2004). The MetS Z‐score will be calculated by adding the MetS risk components for each participant. The MetS Z‐score would be used to measure the change in MetS severity (DeBoer et al., 2018). Further, the effect of the programme on individual MetS markers will also be examined.

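### Safety is assessed as one composite of any adverse events, and that figure alone cannot show whether medical emergencies occurred

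*Protocol article*

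**What the plan says.** Section 2.9.2 (Secondary measures) makes safety part of a secondary outcome: "feasibility of implementation, determined by measures of safety". Section 2.11 (Data collection procedure) says what is collected, namely "subjective reports relative to possible pain, injury, medical emergencies and other" exercise-related complications. Its next sentence states how the information is put together: "Safety and participation rate will be assessed as a composite of any adverse events recorded" on the therapist's checklist and in the participants' exercise diary.

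Section 2.10.6 (Exercise participation and complications) limits the source to the intervention group: "The PT will collect such data from participants in the IG each week", and again at the week-12 follow-up. Section 2.13 (Data analysis) adds only this on the summary: "Feasibility outcomes will be summarised using descriptive statistics such as frequencies, percentages, mean, SD, median and interquartile range".

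The article states no severity grade, seriousness class, separate count of emergencies or safety threshold.

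**The concern.** The listed events differ greatly in weight. Pain after exercise in a previously sedentary person is a matter of tolerability, while a medical emergency bears on whether the programme should go forward at all. Section 2.8.1 spends a long paragraph on preventing hypoglycaemia, so the authors plainly have in mind events unlike ordinary pain. An any-event composite gives both the same weight.

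Safety is one of the two determinants of feasibility in Section 2.9.2, and the Discussion expects the trial to settle whether the programme is feasible before full implementation. If the composite is the safety result, planners of the larger trial could see a high figure that reflects only minor pain, or an ordinary-looking figure that includes several emergencies, and could not tell which they had.

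**Working it through.** **Inputs from the documents.** The number at risk is the intervention group. Section 2.12 gives "the target sample size for this feasibility study will be 90 participants: 45 in each group". This reproduces: 72 / (1 − 0.20) = 90, or 45 per arm. There is no safety figure to reproduce, because no event rate or threshold is stated. Every event rate below is an assumption.

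**Step 1: what the composite can show.** Take the composite as the number of participants with at least one event of any type. This reading is also an assumption, since Section 2.11 names no unit. Each participant then counts once, whatever happened.

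- 22 with pain, 0 emergencies: 22/45 = 48.9%.
- 22 with pain, 3 of whom also had an emergency: 22/45 = 48.9%.
- Emergency rate: 0/45 = 0% against 3/45 = 6.7%.

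Even without overlap, the total does not say which component produced it. This step needs no assumed rate.

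**Step 2: how likely an identical figure is.** If k of 45 report pain and 3 have an emergency independently of pain, the chance that all 3 are already counted for pain is k(k−1)(k−2) / (45 × 44 × 43), where the denominator is 85,140.

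- k = 5: 60 / 85,140 = 0.1%
- k = 9: 504 / 85,140 = 0.6%
- k = 22: 9,240 / 85,140 = 10.9%
- k = 30: 24,360 / 85,140 = 28.6%
- k = 36: 42,840 / 85,140 = 50.3%
- k = 40: 59,280 / 85,140 = 69.6%

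An exactly unchanged figure is therefore possible, but it becomes likely only when most participants report pain.

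**Step 3: how far pain determines the composite.** Let p be the proportion of participants with pain and e = 3/45 = 6.7% the proportion with an emergency, taken as independent. The composite is 1 − (1 − p)(1 − e), and the share of composite-positive participants who have pain is p divided by the composite.

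| Pain rate p | Expected count of 45, no emergencies | Expected count, e = 6.7% | Share with pain |
|---|---|---|---|
| 5% | 2.25 | 5.1 | 44% |
| 10% | 4.5 | 7.2 | 62.5% |
| 20% | 9.0 | 11.4 | 79% |
| 30% | 13.5 | 15.6 | 87% |
| 50% | 22.5 | 24.0 | 94% |
| 70% | 31.5 | 32.4 | 97% |

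At p = 50% the emergencies move the expected count by 1.5, against a standard error of √(45 × 0.533 × 0.467) = 3.35. At p = 5% they move it by 2.85, against a standard error of 2.13. Pain largely sets the figure from about 30% upwards and does not at 5%.

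**Step 4: whether 30% is out of reach.** Section 2.8.1 prescribes 36 sessions. If pain followed a fraction q of sessions, 1 − (1 − q)^36 is 30% at q = 1% and 52% at q = 2%. This assumes independent sessions, the same q for everyone and full attendance. Clustering of pain in some participants, or missed sessions, would lower both figures.

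**Step 5: what separate reporting would show.** For emergencies, 0/45 has a one-sided 97.5% upper limit of 1 − 0.025^(1/45) = 7.9%. For 3/45 the exact 95% interval is 1.4% to 18.3%. These are wide, but they bear on the question being asked.

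**The case against.** The best defence is that the sentence is loosely written and may mean less than it seems to. It names no unit of analysis and no single reported number. It also folds participation rate into a composite of adverse events, although the same section defines participation separately by attendance. It could mean only that events from the checklist and the diary are pooled. Section 2.13 offers frequencies and percentages for feasibility outcomes generally and would permit a table by event type. Grading and table layout are commonly left to a fuller document.

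Much of this limits the point without removing it. Section 2.11 does more than omit detail: it names a composite as the way safety is assessed, and no other section requires a split.

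Two stronger readings are tempting and should be resisted.

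- A reader might infer that exercise soreness is bound to dominate the result. The article never mentions soreness, refers only to possible pain and gives no rate. Steps 2 to 4 show that dominance and identical figures depend on how common pain is and on assumptions of independence, overlap and attendance.
- A reader might infer that emergencies will go unrecorded or be concealed. Complications are collected weekly and at week 12, reasons for withdrawal are documented, and nothing bars the authors from listing emergencies.

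**Conclusion.** The point holds for the measure as Section 2.11 states it. A composite of any adverse events over pain, injury, medical emergencies and other complications cannot, on its own, separate a programme with emergencies from one with only minor pain. That is a matter of construction and rests on no assumed rate, only on reading the composite as a count of participants with any event.

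The size of the masking is conditional. With an assumed 6.7% emergency rate independent of pain, 87% of composite-positive participants have pain when 30% of participants report it, and 94% when 50% do, but 44% when 5% do. The documents do not say where in this range the trial will fall. No figure in the article changes and the primary outcome is untouched. What is affected is the usefulness of the safety half of the feasibility outcome.

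**What to change.** In Section 2.11, replace the composite as the safety measure with separate reporting of the four event types already listed: pain, injury, medical emergency and other complication. Record the type of each event on the existing checklist and diary. For each type give the number and percentage of intervention participants with at least one event, and the number of events. Always show medical emergencies on their own line. An any-event total may be kept as a supplementary line. Injury and emergency should not be merged into a new headline figure, which would again pool unlike events.

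The cost is one classification column and a slightly longer table. Counts per type will be small and their intervals wide, as Step 5 shows. No treatment, schedule or visit changes.

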**FIGURE 1 nop22180-fig-0001:**
[figure not shown]
Participant flow diagram.

### Sample size

2.12

Feasibility studies are designed to obtain preliminary data (Eldridge et al., 2016). Billingham et al. (2013) examined sample size for feasibility RCTs and found a median sample size of 72 (36 per arm). They concluded that while it is important to justify sample size in feasibility RCTs, calculating sample size may not be appropriate. Thus, this proposed study will aim for a sample of 72 participants. To account for attrition, a 20% adjustment will be added. Therefore, the target sample size for this feasibility study will be 90 participants: 45 in each group.

### Data analysis

2.13

Data analysis will be performed using the latest version of STATA. Feasibility outcomes will be summarised using descriptive statistics such as frequencies, percentages, mean, SD, median and interquartile range. Relevant parametric and non‐parametric repeated measure analyses will be undertaken to measure between groups differences and changes in effect between and within the two groups. Specifically, the student's *t*‐test will be used for comparing the IG and CG. Between group analysis will be conducted using Pearson's chi‐square and Mann‐Whitney tests for categorical and continuous variables, respectively. A *p*‐value of <0.05 will be considered statistically significant. To obtain the overall effect of the PA intervention on MetS markers, the MetS score for each participant will be assessed. The MetS score is a useful measure of MetS severity, and it correlates to the severity of CVD (Solymoss et al., 2004). The MetS Z‐score will be calculated by adding the MetS risk components for each participant. The MetS Z‐score would be used to measure the change in MetS severity (DeBoer et al., 2018). Further, the effect of the programme on individual MetS markers will also be examined.

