#### Primary measures

2.9.1

The primary outcome is a change in MetS markers (BP, TG, WC, FBG and HDL) in Ghanaian adults with T2DM who participate in a 12‐week PA programme, compared to those who receive usual diabetes care.

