#### Physical, clinical and biochemical data

2.10.5

Blood pressure and heart rate will be taken during the baseline visit for all participants and during each exercise session at the physiotherapy department for participants in the IG group. Blood pressure will also be measured at the 12‐week follow‐up. WC will be measured at baseline and at the 12‐week follow‐up. A blood sample will be collected at baseline and at the 12‐week follow‐up to measure Fasting Blood Glucose (FBG), high‐density lipoprotein (HDL) and triglycerides (TG).

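### The stated formula for the MetS Z-score, adding the risk components, does not yield a Z-score; the composite for the overall effect needs one explicit definition

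*Protocol article*

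**What the plan says.** Section 2.9.1 (Primary measures) names the markers: "The primary outcome is a change in MetS markers (BP, TG, WC, FBG and HDL". Section 2.13 (Data analysis) then sets out how they are brought together: "To obtain the overall effect of the PA intervention on MetS markers, the MetS score for each participant will be assessed". Two sentences later it gives the construction: the MetS Z-score "will be calculated by adding the MetS risk components for each participant". It gives the purpose as well: the score "would be used to measure the change in MetS severity", with a published source cited for that use. A higher value is therefore meant to be worse.

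The same section applies one significance rule to the analyses ("value of <0.05 will be considered statistically significant") and adds that each marker will also be looked at on its own.

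The article gives no standardisation step, no reference mean or SD and no sign for HDL. It does not say whether systolic or diastolic pressure enters. Section 2.10.5 lists the blood tests without a reporting unit; mg/dL appears only in the glucose rule for exercise sessions (section 2.8.1, Week-1).

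**The concern.** A journal article may leave the details of a score to a fuller document. Here, however, it states a construction rule, and that rule does not give the quantity it names. A Z-score expresses each value as a distance from a reference mean in units of a reference SD, and adding components does neither.

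The score is the stated route to the overall effect on the primary outcome. The Discussion expects the trial to help supply an effect and a variance for a larger one. An analyst who followed the sentence would pass on an effect and a variance set largely by the choice of laboratory unit, with one of the five markers pulling the wrong way. If the definition is settled only once data are in hand, there is also room to choose among versions of the score.

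**Working it through.** The plan gives no figure for the composite to reproduce. Its only computed figure, the target of 90, follows from 72/(1 − 0.20) = 90 and is not affected.

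**Reading 1: measured values are added.**

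*Inputs.* The five markers come from section 2.9.1. The document gives no SDs, so these are assumed: SBP 18 mmHg, WC 11 cm, FBG 60, TG 60 and HDL 14 mg/dL, uncorrelated. Systolic pressure is assumed for BP. To convert mg/dL to mmol/L, divide by 18.016 (glucose), 88.57 (TG) and 38.67 (HDL).

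*Formula.* For uncorrelated components, the variance of the sum is the sum of the squared SDs.

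- mg/dL: 324 + 121 + 3600 + 3600 + 196 = 7841. FBG and TG together: 7200/7841 = 92%.
- mmol/L: the SDs become 3.33 (FBG), 0.68 (TG) and 0.36 (HDL), so the total is 324 + 121 + 11.09 + 0.46 + 0.13 = 456.7. SBP and WC together: 445/456.7 = 97%.
- With the FBG and TG SDs both moved from 40 to 80 mg/dL, the shares run from 83% to 95% (mg/dL) and from 96% to 99% (mmol/L).

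*The order of patients can change with the unit.* The two patients below are invented.

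| | SBP | TG | WC | FBG | HDL | Sum, mg/dL | Sum, mmol/L |
|---|---|---|---|---|---|---|---|
| A | 150 | 150 | 100 | 130 | 40 | 570 | 259.9 |
| B | 130 | 170 | 100 | 145 | 40 | 585 | 241.0 |

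B is the more severe in mg/dL and A is the more severe in mmol/L.

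*Direction of HDL.* If only HDL changes in patient A, from 40 to 45 mg/dL, the sum goes from 570 to 575. An improvement is recorded as greater severity. This needs no assumption about SDs.

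**Reading 2: criteria met are counted.** The unit and HDL problems disappear. The score is then an integer from 0 to 5, and section 2.4 requires MetS at entry, so the low end is not available at baseline. A count is not a Z-score either.

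**Illustration only: standardised terms with HDL left unreversed.** The text does not describe this version. It shows what the sign alone would cost. Suppose each marker improves by d SDs and the components correlate at ρ in the direction of harm.

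- HDL reversed: effect = 5d/√(5 + 20ρ).
- HDL not reversed: effect = 3d/√(5 + 4ρ).
- Ratio = 0.6 × √((5 + 20ρ)/(5 + 4ρ)), which is 0.60, 0.75 and 0.84 at ρ = 0, 0.2 and 0.4.

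The loss in standardised effect is thus about 40%, 25% and 16%, whatever d is.

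**The case against.** The best defence is that the sentence is incomplete wording for a standardised score. It calls the result a Z-score, ties it to severity and cites a source. It does not say that raw values are added or that HDL enters with a positive sign, and a fuller protocol or analysis plan may define all of this. That defence stands as to intent, and it rules out saying that the trial will in fact analyse a raw-unit sum. It does not repair the sentence, because no other section of the article supplies the missing step.

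The stakes are also limited. Every marker is analysed separately, so the primary outcome does not rest on the composite alone. The study is a feasibility trial without a power calculation, and the score can be built from data already to be collected. All of this stands.

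A reader might also infer two competing overall measures, since section 2.13 speaks of both a MetS score and a MetS Z-score. The documents do not establish that: the terms occur in close sequence for the same purpose and can be a short and a long name for one thing. The uneven naming is worth tidying, no more.

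**Conclusion.** The concern holds as a defect in the stated definition of the composite. Neither reading of the sentence gives a Z-score, and the literal reading gives a unit-dependent sum in which better HDL counts as worse disease. Those conclusions follow from the text alone. The variance shares of about 92% and 97% rest on assumed SDs and zero correlation.

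A reader might go further and conclude that the trial's main result is invalid, or that 40% of the effect and much of the power will be lost. The documents do not support this. The markers are examined individually, and the sample size was not derived from power. The 40% loss applies to the standardised effect only at zero correlation, in a standardised but unreversed score that the plan does not describe.

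**What to change.** Replace the construction sentence in section 2.13 with one explicit definition, fixed before the week-12 data are examined. Either of these would do:

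- Name and apply the published severity equation that the plan already cites.
- Define the score as a sum of components, each standardised with the same baseline mean and SD at both visits, with HDL subtracted. State which blood pressure measure enters and whether TG is transformed.

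The second is one of several sound constructions, so the choice belongs to the authors. Use a single name, MetS Z-score, throughout. The cost is about two sentences, with no new data, visits or change to the sample size.

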### Ethical review

2.14

Ethics approvals for the study were sought from the following institutions: Institutional Review Board of the Korle‐Bu Teaching Hospital (protocol ID number: KBTH‐IRB/00011/2022) and the Deakin University Human Research Ethics Committee (Project Number 2022‐041). The trial is registered in the Australian New Zealand Clinical Trial Registry (registration number: ACTRN12622000323729p). This study is guided by the Consolidated Standards of Reporting Trials (CONSORT).

## EXPECTED RESULTS

3

It is expected that this trial will provide preliminary data regarding the feasibility and safety of the PA programme for Ghanaian adults with T2DM. It will also provide data on outcomes that will inform the design of a future large‐scale RCT.

## DISCUSSION

4

Interventions aimed at controlling MetS markers in people with T2DM are a priority (Longo‐Mbenza et al., 2010). Despite the integral role PA plays in modifying MetS markers, the problem of meeting recommended PA targets remains a challenge for people with T2DM (Oyewole et al., 2014). A significant proportion of Ghanaian adults with T2DM may be considered high‐priority population due to some health beliefs that influence their health‐seeking behaviours, including PA uptake. For instance, Korsah et al. (2022), in assessing the experiences and cultural beliefs of Ghanaians with diabetes, found that some people perceive their diabetes diagnosis as a spiritual disease that can only be treated through spiritual healing. There is also some evidence that many people in Ghana first seek herbal and faith‐based treatment and only resort to biomedical treatment when the disease persists (Arias et al., 2016). These evidences suggest that PA is perceived as less important in managing diabetes. The education component of the PA programme to be evaluated in this study aims at addressing the poor understanding and other barriers that exist in engaging in a PA programme. Also, lack of access to exercise facilities and the cost to access them appear to be major barriers to PA uptake (Higgerson et al., 2018). The PA programme to be evaluated is expected to be suitable for people in low‐resource communities because it is home‐based with no access cost.

A feasibility RCT is usually intended to guide the planning of a future definitive investigation, as it helps to establish an effect and variance (Thabane et al., 2010). This study has the potential to provide information on efficacy, intervention participation and safety (Eldridge et al., 2016; Thabane et al., 2010). Thus, the findings will inform future trials on study design, relevant resources, trial personnel and data management (Thabane et al., 2010). The results of this feasibility study will provide preliminary evidence regarding the effect of a culturally appropriate PA programme and whether it will show a trend towards improvement in MetS markers and QoL in Ghanaian adults with T2DM. The findings of this study will also prove the feasibility or otherwise of the PA programme, prior to its full implementation in the population.

